## Objectives

The primary objective of this study is to determine the annual prevalence of 17-year-old patients living in the city of Nice who consult specialised CAMHS child and adolescent psychiatry services, relative to the total population of 17-year-olds residing in Nice.

The secondary objectives are to:

Estimate the annual prevalence of 17-year-olds living in Nice who consult specialised CAMHS (Nice University Children’s Hospital(HPU Lenval)), relative to the population of minors (<18 years) in psychiatric clinical care.Describe the clinical and sociodemographic profiles of a sample of 17-year-old patients living in Nice and consulting specialised CAMHS (HPU Lenval).Characterise care trajectories over a 12-month follow-up period, according to the evolution of clinical management.Assess the clinical course of patients during follow-up.Evaluate the level of readiness for transition to adult psychiatry.Identify factors associated with continuity of psychiatric care at 12 months.

Taken together, these objectives aim to generate actionable local evidence to tailor transition planning and service organisation to the specific needs of young people in Nice. Findings will inform locally adapted tools and dedicated pathways to improve continuity of care across the CAMHS–AMHS transition.

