#### Inclusion criteria

Participants must meet all of the following criteria:

Age ≥17 and <18 years at inclusion.Receiving care (outpatient, inpatient or emergency) within the Child and Adolescent Psychiatry Department at Lenval University Children’s Hospital.Presence of a psychiatric disorder according to Diagnostic and Statistical Manual of Mental Disorders, Fifth Edition (DSM-5) criteria, irrespective of diagnostic category.Considered to be in a potential transition situation to adult mental health services within the following 12 months.Living in the municipality of Nice (postal codes 06000, 06100, 06200, 06300).Able to provide written informed consent, together with at least one parent or legal guardian.

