#### Secondary outcomes

Annual prevalence of 17-year-old patients living in the municipality of Nice who attend the child and adolescent psychiatry services (Lenval University Children’s Hospital) in 1 year, expressed as the proportion of these patients relative to the total number of minors (<18 years) consulting in the hospital during the same year (psychiatric clinical population).Baseline description of patient profiles in the prospective cohort (n=100), including sociodemographic and medical characteristics.Care trajectories at 12 months, categorised as:Continued care in child and adolescent psychiatry.Transfer to adult psychiatry.Discontinuity or interruption/resumption of care during follow-up.Care formally discontinued in agreement between patient and care team.Lost to follow-up.Clinical evolution assessed using the MINI questionnaire at baseline (M0), 6 months (M6) and 12 months (M12), focusing on status. Additional outcomes include quality of life (WHOQOL-BREF) and care needs/psychosocial difficulties (HoNOSCA) scores at the same time points.Readiness and outcome of transition: measured with the TRAM at M0 and M6, and the TROM at M12.Continuity of psychiatric care at 12 months, defined as ‘effective’ if the patient has a structured care plan in place or has recovered and no longer requires follow-up. This binary outcome (yes/no) will be determined by the investigator based on patient evaluation. Predictors of continuity will include prespecified baseline variables selected on clinical relevance and prior literature, including sex, living situation, psychiatric history, current diagnostic profile (MINI-S), quality of life (WHOQOL-BREF), care needs and psychosocial difficulties (HoNOSCA) and transition readiness (TRAM).

Active recontact procedures (phone/SMS/email reminders and, when relevant, parental contact) will be used to limit attrition. Participants will be considered lost to follow-up only if no contact can be re-established and no information on ongoing care can be obtained.

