### Measures

#### Sociodemographic and medical data: 

Baseline information will include living situation, schooling/occupation, care pathways, psychiatric and medical history and treatment exposure. These variables are collected from clinical records and participant report to characterise the study population and explore factors associated with continuity of care during the transition period.

#### 
MINI-S (DSM-5; French V.1.2):

The MINI-S is a brief, structured diagnostic interview aligned with DSM-5, designed for administration by clinicians trained in DSM-5 criteria. The adult version is applicable from age 17. The instrument has established reliability and validity and has been validated in both French and English.^26
27^ In this study, the MINI-S will be administered at M0, M6 and M12 to assess current (present-state) diagnoses and symptom status. We will use diagnostic modules and summary indicators; item-level data will not be modelled in multivariable analyses

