#### Secondary outcomes

Prevalence relative to the broader clinical population of minors (<18 years) attending Lenval psychiatry services.Patient profiles at baseline: descriptive statistics for sociodemographic and clinical variables.Care trajectories over 12 months: described using absolute and relative frequencies.Clinical assessments (MINI-S, WHOQOL-BREF, HoNOSCA): summarised at baseline, 6 months and 12 months; visualised using histograms and line graphs.Transition readiness (TRAM) and outcomes (TROM): summarised with means, SD, medians and IQRs; visualised by domains.

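### Clinical evolution is planned as status summarised visit by visit, with no within-patient measure, so it cannot separate persistence, remission and new onset within a diagnosis

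*Protocol article*

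**What the plan says.** The Objectives section includes: "Assess the clinical course of patients during follow-up".

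Under Outcomes, the secondary outcome for this objective is "Clinical evolution assessed using the MINI questionnaire at baseline (M0), 6 months (M6) and 12 months (M12), focusing on status". It continues: "Additional outcomes include quality of life (WHOQOL-BREF) and care needs/psychosocial difficulties (HoNOSCA) scores at the same time points".

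The MINI-S entry under Measures explains that "the MINI-S will be administered at M0, M6 and M12 to assess current (present-state) diagnoses and symptom status", and on the level of analysis: "We will use diagnostic modules and summary indicators; item-level data will not be modelled in multivariable analyses".

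The Statistical analysis section gives one line on the matter: "Clinical assessments (MINI-S, WHOQOL-BREF, HoNOSCA): summarised at baseline, 6 months and 12 months; visualised using histograms and line graphs". The article states no change score, transition table, or definition of remission or onset.

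Four other places bear on how the result would be read:
- The inclusion criteria require "Presence of a psychiatric disorder according to Diagnostic and Statistical Manual of Mental Disorders, Fifth Edition (DSM-5) criteria, irrespective of diagnostic category".
- The Missing data section rules out imputation and promises unspecified sensitivity analyses.
- The strengths and limitations list says that attrition could be related to clinical severity or disengagement.
- The Discussion acknowledges that there is no control group.

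**The concern.** The objective asks what happens to patients over a year. The stated analysis describes how many are in a given state at each visit. These are different quantities. A flat line for a diagnosis can mean that the same patients stayed ill, or that many recovered while as many others became ill. The Introduction describes disorders in this age group as emerging and often crossing diagnostic boundaries, so movement between diagnoses is what a transition service would want to learn from this cohort.

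Two further features make the line graphs hard to read. First, if patients drop out and nothing is imputed, a difference between visits mixes change in patients with change in who was assessed. Second, all patients enter with a disorder. Ordinary fluctuation or re-rating differences in overall diagnostic status will therefore tend to appear as improvement from baseline, and no comparison group can show how much of it is that.

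**Working it through.** The plan gives no figure for this outcome: no expected MINI-S frequency, effect size or power, and the cohort size of 100 is feasibility-based. There is nothing to reproduce. The check asks what the planned summaries can and cannot identify. All margins below are assumptions chosen for illustration.

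**1. One diagnostic module, n = 100, no attrition.** Let a be the number positive at M0, b the number positive at M12, and k the number positive at both. The visit summaries give a and b but not k, which is bounded by

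max(0, a + b − 100) ≤ k ≤ min(a, b).

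Remissions = a − k and onsets = b − k.

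| a (M0) | b (M12) | k | Remissions | Onsets |
|---|---|---|---|---|
| 40 | 40 | 0–40 | 0–40 | 0–40 |
| 40 | 30 | 0–30 | 10–40 | 0–30 |
| 40 | 50 | 0–40 | 0–40 | 10–50 |

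In the first row, the remission proportion among baseline-positive patients can be anything from 0/40 = 0% to 40/40 = 100%. These are logical bounds, not likely values. They show that the summary carries almost no information on the question.

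**2. Attrition without imputation.** Assume 40 of 100 positive at M0, no patient changes state, and 20 patients are missing at M12.
- If all 20 lost were positive, M12 shows (40 − 20)/80 = 25%.
- If all 20 lost were negative, M12 shows 40/80 = 50%.

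The visit summary thus moves from 40% to somewhere between 25% and 50% with no change in any patient. A paired table among the 80 assessed twice would show no remissions and no onsets.

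**3. Selection at entry.** Let c be the proportion positive at M0 on an overall indicator of diagnostic status. The later proportion exceeds c only if

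(1 − c) × onset risk > c × remission risk, that is, onset risk / remission risk > c/(1 − c).

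- c = 0.90: ratio above 0.90/0.10 = 9
- c = 0.80: ratio above 0.80/0.20 = 4
- c = 0.70: ratio above 0.70/0.30 = 2.3

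A fall from baseline is therefore the likelier direction whenever entry makes c high. A rise remains possible if c is below 1. For example, 85 to 90 positive fits 5–15 onsets with 0–10 remissions.

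**The case against.** The strongest reply is that this is a condensed article. The same patients have the same interview three times, so persistence, remission and onset can all be derived, and the one-line analysis description does not forbid cross-tabulation. A fuller protocol or SAP, not seen here, may contain it. The outcome is descriptive, and WHOQOL-BREF and HoNOSCA, which can move either way, also describe clinical course. This stands in part: the data and design are sound and the gap is confined to the stated analysis. But the article does more than stay silent. It defines clinical evolution as status and names the analysis, and that analysis, followed as written, does not answer the objective. The WHOQOL-BREF and HoNOSCA scores are to be summarised by visit in the same way.

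A reader might go further and infer that the proportion with any disorder can only fall. The document does not support that:
- It names no any-disorder endpoint. It refers to diagnostic modules and summary indicators, and single modules can rise.
- Entry is by DSM-5 criteria and is not stated to require a positive MINI-S, so baseline positivity may be below 100%.
- Even from 100% at M0, the count can rise between M6 and M12. Going from 60 to 75 of 100 fits 15–40 onsets and 0–25 remissions.
- If all 100 were positive at M0, a drop to 70 would mean exactly 30 without a disorder and no first onsets. The remission/onset ambiguity therefore arises for single modules, or when baseline is below 100%, and not where a strict ceiling applies.

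The exclusion of acute or unstable cases and the 72-hour reflection period also reduce recruitment at peak severity, so the selection effect is softened, though not removed.

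**Conclusion.** The point holds for the stated analysis. Clinical evolution is fixed as status at each visit, and for a given module those summaries cannot separate persistence, remission and new onset. With 40 of 100 positive at both M0 and M12 (assumed margins), 0 to 40 of each is compatible. Without imputation, the visits may also describe different patients.

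The selection issue is a matter of interpretation only: a decline in overall diagnostic status from M0 is partly expected because entry requires a disorder and there is no control group. Its size cannot be derived from the document. The document gives no ground for saying that a fall is certain, or that the authors intend to report one as improvement.

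The weight is minor to moderate. This is a secondary, descriptive outcome, and the remedy uses data already planned.

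**What to change.** In the Statistical analysis section, under secondary outcomes, keep the visit summaries and add a within-patient analysis among patients assessed at both visits:

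- For the main MINI-S diagnostic groups, tabulate persistent, remitted, newly present and never present, for M0 to M6 and for M0 to M12. Give 95% CIs for remission among baseline-positive patients and for onset among baseline-negative patients.
- For the WHOQOL-BREF domains and the HoNOSCA total, report mean within-patient change with 95% CI over the same intervals.
- State the number of patients behind each comparison, and add a sentence that a decline in overall diagnostic status from M0 is partly expected from the entry criterion.

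The cost is analysis wording and a few tables, with no new assessment. The downside is sparse cells. At an observed 50% remission, the approximate 95% half-width is 1.96 × √(0.25/40) = 15 to 16 percentage points with 40 baseline-positive patients, and 1.96 × √(0.25/10) = 31 points with 10. The tables should therefore be limited to the common diagnostic groups and not split by care setting, which also fits the article's intention to work with composite and domain-level measures. Paired tables remove the mixing of different patients between visits, but they do not correct for selective dropout, so the planned comparison of completers with those lost is still needed.

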### Measures

#### Sociodemographic and medical data: 

Baseline information will include living situation, schooling/occupation, care pathways, psychiatric and medical history and treatment exposure. These variables are collected from clinical records and participant report to characterise the study population and explore factors associated with continuity of care during the transition period.

#### 
MINI-S (DSM-5; French V.1.2):

The MINI-S is a brief, structured diagnostic interview aligned with DSM-5, designed for administration by clinicians trained in DSM-5 criteria. The adult version is applicable from age 17. The instrument has established reliability and validity and has been validated in both French and English.^26
27^ In this study, the MINI-S will be administered at M0, M6 and M12 to assess current (present-state) diagnoses and symptom status. We will use diagnostic modules and summary indicators; item-level data will not be modelled in multivariable analyses

#### WHOQOL-BREF:

The WHOQOL-BREF is a validated 26-item questionnaire developed by the WHO that yields four domain scores—physical, psychological, social relationships and environment—plus two global items. Items are rated on 5-point Likert scales and transformed to 0–100 domain scores per WHO guidance.^28^ The French version has been validated and used in both general and psychiatric populations,^29^ with good psychometric properties and cross-cultural validity. The WHOQOL-BREF will be administered at M0, M6 and M12; analyses will focus on domain-level scores.

#### HoNOSCA:

HoNOSCA is a 13-item clinician-rated scale (0–4 per item; higher scores indicate greater difficulties) covering behavioural, emotional, social, somatic and functioning problems, and is commonly used to assess care needs and monitor clinical change in routine child and adolescent mental health services.^30^ A validated French self-report version (F-HoNOSCA-SR) is also available^31^ and may be used to complement clinician ratings where feasible. HoNOSCA will be administered at M0, M6 and M12; analyses will use total and selected domain subscores.

#### TRAM:

Developed within the Managing the Link and Strengthening Transition from Child to Adult Mental Healthcare in Europe (MILESTONE) programme, the TRAM is a validated multidimensional measure assessing the appropriateness and readiness for transition from child/adolescent to adult mental health services.^32
33^ It covers symptom frequency/severity, global illness impact, daily functioning impact, risk behaviours, diagnostic complexity/factors and satisfaction with care. To maximise feasibility, only the patient-reported version will be used in this study. TRAM will be administered at M0 and M6; analyses will prioritise the total readiness/appropriateness indices and a restricted set of prespecified subscales.

#### TROM:

The TROM, also validated within MILESTONE,^34^ evaluates the quality and outcomes of the transition process, including clinical status, service use/engagement and satisfaction. It will be administered at M12 (end of follow-up) to capture post-transition outcomes. Analyses will focus on the global outcome index and a limited number of predefined subscales.

Given the planned sample size (n=100), analyses will focus on composite indices and domain-level scores from each instrument, rather than item-level data. Only the most clinically and methodologically relevant variables will be retained for multivariable models to reduce the risk of over-parameterisation

### Sample size estimation

Reliable local prevalence data on 17-year-olds at the transition boundary between child and adult mental health services are currently lacking. The present study addresses this gap through an epidemiological component based on INSEE census counts and PMSI hospital discharge data.

For the prospective cohort, the target sample size (n=100) was determined a priori using a feasibility-based approach. It was informed by the annual number of 17-year-olds receiving psychiatric care at Lenval University Children’s Hospital (approximately 160–200 per year), expected consent and participation rates observed in previous local non-interventionnal studies involving human participants (Recherche Impliquant la Personne Humaine, category 3 under the French regulatory framework), and the practical feasibility of recruitment within an 18-month inclusion period. This sample size is expected to provide adequate precision for descriptive estimates of clinical and sociodemographic characteristics and to support exploratory multivariable analyses examining factors associated with continuity of care at 12 months. Given the exploratory nature of secondary analyses, effect-size assumptions for formal power calculations were not available; therefore, sample size was primarily driven by feasibility and the objectives of estimation and model exploration.

### Statistical analysis

All analyses will be conducted by a biostatistician from the Clinical Research Department of Nice University Hospital using SAS Enterprise Guide V.7.1 (SAS Institute, Cary, North Carolina, USA). A two-sided p value <0.05 will be considered statistically significant, unless otherwise specified. Assumptions underlying statistical tests will be systematically verified prior to use.

#### Descriptive analyses

 Baseline characteristics of the study population will be summarised using absolute and relative frequencies (with 95% CIs) for categorical variables, and means (±SD), medians and IQRs for quantitative variables. A flow chart will present the number of patients included and followed at each stage.

#### Primary outcome

 The annual prevalence of 17-year-old patients living in Nice who attend child and adolescent psychiatry services at Lenval University Children’s Hospital will be calculated as the ratio of the number of patients attending services to the total number of 17-year-olds in the general population of Nice, with 95% CIs.

#### Secondary outcomes

Prevalence relative to the broader clinical population of minors (<18 years) attending Lenval psychiatry services.Patient profiles at baseline: descriptive statistics for sociodemographic and clinical variables.Care trajectories over 12 months: described using absolute and relative frequencies.Clinical assessments (MINI-S, WHOQOL-BREF, HoNOSCA): summarised at baseline, 6 months and 12 months; visualised using histograms and line graphs.Transition readiness (TRAM) and outcomes (TROM): summarised with means, SD, medians and IQRs; visualised by domains.

#### Continuity of care analyses

 Continuity of psychiatric care at 12 months (binary outcome: defined care plan vs no defined plan) will be examined using logistic regression. Univariate logistic models will first be applied; variables associated with continuity of care at p<0.20 will be considered for inclusion in a multivariable logistic regression model. Results will be reported as ORs with 95% CIs. Collinearity will be assessed prior to multivariable modelling. Given the planned sample size (n=100), multivariable models will be restricted to a limited number of prespecified variables selected on the basis of clinical relevance and previous literature, including sex, living situation, psychiatric history, baseline diagnostic profile (MINI-S), quality of life (WHOQOL-BREF), care needs and psychosocial difficulties (HoNOSCA) and transition readiness (TRAM), in order to reduce the risk of overfitting and ensure robustness of results.

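### The 12-month continuity outcome is worded in two ways, and the regression wording leaves out patients who have recovered

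*Protocol article*

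**What the plan says.** Under Outcomes, Secondary outcomes, continuity of psychiatric care at 12 months is "defined as ‘effective’ if the patient has a structured care plan in place or has recovered and no longer requires follow-up". The same paragraph says how it is coded and by whom: "This binary outcome (yes/no) will be determined by the investigator based on patient evaluation".

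Under Statistical analysis, Continuity of care analyses, the variable with the same name and time point reappears with different levels: "Continuity of psychiatric care at 12 months (binary outcome: defined care plan vs no defined plan) will be examined using logistic regression". Recovery is not mentioned there. The paragraph then sets out univariate logistic models, a p<0.20 screen, and a multivariable model drawing on sex, living situation, psychiatric history, MINI-S profile, WHOQOL-BREF, HoNOSCA and TRAM.

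The Outcomes section also lists, among the care trajectories, "Care formally discontinued in agreement between patient and care team". The plan therefore expects some patients to leave care properly rather than by dropping out.

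**The concern.** The two statements share a name, a time point and a binary form, but they do not sort patients in the same way. They differ on one group: patients who are well at 12 months, need no further care and so have no plan. The Outcomes section counts them as successes. The levels given for the regression leave them only the no-plan side, together with those who disengaged.

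Continuity is the only outcome for which the article specifies a regression; the other cohort outcomes are to be summarised descriptively. It carries the objective of identifying factors associated with continuity, and the Discussion hopes the results will help to identify patients at risk of disengagement. Patients who recover probably differ at baseline on HoNOSCA, WHOQOL-BREF and diagnostic profile, all of which are candidate predictors. Moving them between outcome levels would then not be random with respect to the predictors. It could change both which variables pass the p<0.20 screen and what the fitted odds ratios mean.

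**Working it through.** **Step 1: compare the definitions patient by patient.**

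| Status at 12 months | Outcomes section | Regression paragraph, read literally |
|---|---|---|
| Plan in place | yes | plan |
| Recovered, no further care needed, no plan | yes | no plan |
| Neither | no | no plan |

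Only the middle row differs. The article contains no sentence saying that recovery counts as a plan, or that one definition takes precedence.

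**Step 2: is there a figure to reproduce?** No. The planned cohort is 100. The Sample size estimation section says the number was driven by feasibility and gives no expected rate of continuity, recovery or drop-out. Everything below uses assumed counts and complete 12-month data, and serves only to show what the coding can do.

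**Step 3: effect on the split.** Assume that 50 of 100 have a plan and r have recovered without one. Successes are 50 + r under the Outcomes section and 50 under the regression paragraph.

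- r = 5: 55/45 against 50/50
- r = 10: 60/40 against 50/50
- r = 20: 70/30 against 50/50

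So r patients, here 5 to 20, change level.

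**Step 4: effect on an odds ratio.** Take 50 patients with low and 50 with high baseline severity. Let P be the number with a plan and R the number recovered without one. The odds of success in a group are (P + R)/(50 − P − R) under the Outcomes section and P/(50 − P) under the regression paragraph. The odds ratio is low over high severity.

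| Assumed P, low vs high | Assumed R, low vs high | OR, Outcomes section | OR, regression paragraph |
|---|---|---|---|
| 25 vs 25 | 8 vs 2 | (33/17)/(27/23) = 1.65 | (25/25)/(25/25) = 1.00 |
| 22 vs 28 | 8 vs 2 | (30/20)/(30/20) = 1.00 | (22/28)/(28/22) = 0.62 |
| 22 vs 28 | 15 vs 5 | (37/13)/(33/17) = 1.47 | (22/28)/(28/22) = 0.62 |
| 25 vs 30 | 15 vs 3 | (40/10)/(33/17) = 2.06 | (25/25)/(30/20) = 0.67 |

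In all four rows the literal regression coding gives the lower odds ratio for low severity. In the first two rows an association disappears or appears. In the last two the direction reverses, and both of those rows assume fewer plans in the low-severity group together with more recoveries.

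**The case against.** The best defence is that there is only one variable. The Outcomes section gives the formal definition, the coding and the assessor; the regression paragraph uses the same name and adds a short gloss in brackets. That gloss may be shorthand, or an agreed discharge may be regarded as a defined plan. On either view the investigator records one yes/no answer and the model uses it. This stands in part. A reader might infer that the protocol deliberately codes recovered patients as failures, and the text does not say so; that result follows only from reading the two levels literally. But the article does not state either benign reading, and a statistician who programmed the outcome from the analysis paragraph would have no reason to add recovery.

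A reader might also infer a second contradiction, between the binary outcome and the trajectory category "Discontinuity or interruption/resumption of care during follow-up": a patient who left care and came back could fall there and still count as effective continuity. The documents do not support this. The trajectory describes what happened over the follow-up period and the binary outcome describes status at its end, so both can be true of one patient. How overlapping trajectory categories are allocated is detail that an article may leave to the full protocol or the analysis plan.

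Finally, the odds ratios rest on invented counts, and the analysis is exploratory and belongs to the last-listed secondary objective. Both points are correct. They limit the weight of the finding but do not remove the mismatch.

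**Conclusion.** The point holds as an inconsistency between two stated definitions of one outcome. It is not a matter of detail left out: both definitions are in the article, and they classify recovered patients without a plan differently.

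Its size cannot be determined. It depends on how many patients recover without a plan and on how strongly recovery relates to the baseline predictors, and the documents quantify neither. Reversal of an odds ratio is possible under some assumed counts; a reader should not take it as the expected result. With equal plan rates in the two groups, the example gives an association lost rather than reversed.

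The consequence is confined to the secondary, exploratory analysis of factors associated with continuity. The primary outcome, prevalence from administrative and census data, does not use this variable.

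**What to change.** In Continuity of care analyses, replace the bracketed levels with the definition from the Outcomes section: effective continuity "if the patient has a structured care plan in place or has recovered and no longer requires follow-up", against neither of these. State that the modelled variable is the investigator's yes/no determination under that definition. If an agreed discharge without recovery is meant to count as a plan, say so in both places.

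The binary outcome should not be rebuilt from the trajectory categories. An agreed end to care is not the same as recovery, and such a mapping would replace the investigator's determination. It would also need new rules for patients who returned after a gap and for those lost to follow-up.

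The cost is one line in the protocol and the matching line in any analysis plan, with no extra patients, visits or data items. Recruitment started on 7 April 2026, so 12-month visits fall due from about April 2027. The wording should be settled before those data are analysed, so that the coding cannot be chosen in the light of results.

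### The univariate p<0.20 screen undercuts the prespecification meant to protect the continuity-of-care model, and 7 to about 14 candidate parameters on at most 50 events do not support the robustness claim

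*Protocol article*

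**What the plan says.** The protocol article, Continuity of care analyses, starts with univariate logistic models and then states that "variables associated with continuity of care at p<0.20 will be considered for inclusion in a multivariable logistic regression model". Later in the same paragraph, "multivariable models will be restricted to a limited number of prespecified variables selected on the basis of clinical relevance and previous literature". That restriction is said to lower the risk of overfitting and to secure robust results.

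Seven constructs are named: sex, living situation, psychiatric history, MINI-S diagnostic profile, WHOQOL-BREF, HoNOSCA and TRAM. The list is introduced as examples, so it is not closed, and no parameter count is given. The Secondary outcomes section calls these predictors prespecified and mentions no screen. For WHOQOL-BREF, "analyses will focus on domain-level scores", of which there are four. The HoNOSCA section allows a total plus selected subscores, and the TRAM section allows indices plus subscales.

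On size, "the target sample size (n=100) was determined a priori using a feasibility-based approach", and "effect-size assumptions for formal power calculations were not available". The sample is nevertheless expected "to support exploratory multivariable analyses examining factors associated with continuity of care at 12 months". No event rate, attrition rate or parameter cap is given for this model.

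**The concern.** Prespecification protects a model because the outcome has no say in which terms enter. A univariate p-value screen gives the outcome that say. The paragraph does not state which rule governs, or whether a prespecified variable with p of 0.20 or more is dropped. The number of candidates examined also stays the same after screening, while the final model's confidence intervals are computed as if only the survivors had ever been considered.

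At stake is the objective on factors associated with continuity. The Discussion expects the project to help identify patients at risk of disengagement. Odds ratios that are too far from 1, intervals that are too narrow and real predictors lost at the screen would all feed into that use.

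**Working it through.** There is no calculation behind n=100 to reproduce, because it was set by feasibility.

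**1. Candidate parameters**
- One per construct: 7.
- Four WHOQOL-BREF domains instead of one score: 7 + 3 = 10.
- An assumed fuller coding: sex 1, living situation 2, psychiatric history 1, MINI-S 3, WHOQOL-BREF 4, HoNOSCA 1, TRAM 2 = 14.

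**2. Events per candidate parameter**

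Limiting events = min(n·p, n·(1−p)). The ceiling at n=100 is 50, whatever the true rate. The study states no rate of its own. The Introduction cites about 60% with disrupted care and 50% discontinuing, which suggests 40-50 events without loss. The 20% loss below is assumed.

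| n | Outcome rate | Limiting events | 7 parameters | 10 | 14 |
|---|---|---|---|---|---|
| 100 | 50% | 50 | 7.1 | 5.0 | 3.6 |
| 100 | 40% or 60% | 40 | 5.7 | 4.0 | 2.9 |
| 80 | 50% | 40 | 5.7 | 4.0 | 2.9 |
| 80 | 40% or 60% | 32 | 4.6 | 3.2 | 2.3 |

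**3. What passes the screen**
- Null variables expected to pass: 0.20 × 7 = 1.4, or 0.20 × 14 = 2.8.
- Probability that at least one passes, if independent: 1 − 0.8^7 = 79%, or 1 − 0.8^14 = 96%.
- Real predictor with odds ratio 2 (balanced binary, 40% base rate): the odds 0.667 become 1.333, so the rates are 40% and 57.1%. Power at two-sided alpha 0.20 is 67% with 100 patients and 60% with 80, so it is dropped 33% or 40% of the time.

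**4. Interval coverage after screening, no real predictor**

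A null term that passes has a p-value spread evenly between 0 and 0.20. If the multivariable p-value is close to the univariate one, its 95% interval excludes 1 with probability 0.05/0.20 = 25%, so coverage is about 75%. Simulation agrees: with independent predictors, a 45% outcome rate, 7 or 14 candidates and 80 or 100 patients, coverage is 76-77%. Adding settings with predictors correlated at 0.3 widens the range to about 76-88%. Fitting all candidates without the screen gives about 94-95%.

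**5. Real predictors (three, odds ratio 1.5 per SD)**
- Independent predictors: retained log odds ratios are inflated about 1.3-1.5-fold, against 1.1-1.3-fold unscreened.
- Correlation 0.3, 14 candidates, 80 patients: inflation is 1.08 screened against 1.37 unscreened, and screened coverage is 96%. The harm from the screen largely disappears.

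**6. Is the screen the cause of overfitting?**

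For 14 candidates, screened against all fitted:

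| Measure | Screened | Unscreened |
|---|---|---|
| Calibration slope, three real predictors | 0.37-0.53 | 0.25-0.32 |
| At least one p<0.05, no real predictor | 26-48% | 54-57% |

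The slope is far below 1 either way, and it is worse without the screen. The load of candidates on few events drives the overfitting. A small fixed model with one score per instrument and a penalised fit restored nominal coverage and raised the slope to 0.58-0.67.

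**The case against.** The strongest defence is that the paragraph is coherent: candidates are prespecified, screened within that list, and only considered for inclusion. That reading is available. A reader might infer an outright contradiction between the two rules, and the documents do not support that. It is an unreconciled tension in which the second step weakens the first.

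A reader might also take 14 parameters as the plan's number. It is not. The TROM section promises composite indices and domain scores, with only the most relevant variables retained, and final coding is commonly left to an analysis plan. The range from 7 upward is what can be supported, and even 7 gives no more than 7.1 events per parameter.

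Third, the screen is not the source of overfitting and does not raise the chance of a false positive. Against the same candidates unscreened it lowered both the false-positive rate and the miscalibration. That part of the defence stands in full.

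Finally, the analyses are labelled exploratory and the Discussion concedes limited multivariable power. This limits the consequence, but it does not answer the point. Low power is different from intervals that do not cover at their stated level, and the article still applies a general threshold: "A two-sided p value <0.05 will be considered statistically significant".

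**Conclusion.** The point holds in a limited form. The p<0.20 step lets the outcome choose a model whose robustness is credited to prespecification, and the robustness claim is stronger than 100 patients can support. The size depends on assumptions. The 50-event ceiling is arithmetic, but 40-50 events and 20% loss are not planning figures of this study. The cited background rates also describe a different outcome, since this study counts recovered patients who need no follow-up as continuity. Under-coverage was shown for settings with no real predictor and the extra inflation for independent predictors; clinical scales are likely to be correlated, which softens both.

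A reader might infer that deleting the screen would be enough. It would not: seven parameters without a screen still leave 5.7-7.1 events each with no loss and 40-50 events. Only the exploratory secondary objective on continuity of care is affected; the primary prevalence outcome is not.

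**What to change.** In Continuity of care analyses:

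- Delete the p<0.20 step.
- Fix one model in advance from the listed predictors, with one score per instrument and a stated cap. At the conventional 10 events per parameter (not a figure from the documents), 40-50 events allow 4-5 parameters; 32 events would allow about 3. Since seven constructs are named, the sponsor must choose among them before outcomes are analysed.
- Fit it by Firth penalised likelihood, which SAS PROC LOGISTIC provides.
- Report the remaining candidates as unadjusted odds ratios only.
- Replace the closing claim of robust results with exploratory wording.

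The cost is a change of wording and fewer adjusted odds ratios. Recruitment is still under way, so the change can be made before any 12-month outcome is analysed.
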